#### Secondary outcome measures

##### Cognitive function

A test battery based on the Minimal Assessment of Cognitive Function in MS (MACFIMS) will be used [41]. Verbal learning and memory is assessed with the Dutch version of the California Verbal learning Test (CVLT) [42]. Spatial learning and memory are measured with the Brief Visuospatial Memory Test-Revised (BVMT-R) [43]. Visual-spatial abilities are measured with the Benton Judgment of Line Orientation Test (JLO) [44]. Visual processing speed and working memory are measured with the Symbol Digit Modalities Test (SDMT) [45]. Verbal fluency and memory retrieval are assessed with the Controlled Oral Word Association Test (COWAT) [46]. Higher executive function is measured with the Delis-Kaplan Executive Function System sorting test (D-KEFS) free sorting condition [47]. Selective attention and response inhibition are measured with the Stroop Colour-Word Test [48]. When available, parallel versions of tests will be administered for repeated assessment to account for material-specific learning effects.

##### Functional brain networks

Resting-state MEG data will be recorded using a 306-channel whole-head MEG system (Elekta Neuromag Inc., Helsinki, Finland) in a magnetically shielded room (Vacuumschmelze GmbH, Hanau, Germany) at the VU University Medical Center. Magnetic fields will be recorded during resting state (i.e. a no-task, eyes-closed condition). Pre-processing of data and removal of noise will be done on Linux computers with available scripts [49]. The MEG data will be used to determine resting-state functional connectivity and brain network organisation. To study functional connectivity, synchronisation measures will be computed, such as the phase-lag index [7, 50]. To study brain network organisation, tools from modern network theory will be applied to the entire network and a subset of the network (i.e. the minimum spanning tree (MST)) [8, 50]. Measures such as degree, clustering coefficient and path length will be computed, as well as MST-network derived measures, such as betweenness centrality, tree hierarchy and eccentricity. There will be an emphasis on node centrality measures to identify the ‘hubs’ (i.e. highly connected nodes) of the network [51]. Since the field of modern network science is constantly developing, the best methods and measures will be selected once the study is completed.

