**Methods/design:**

In a dual-centre, single-blind randomised controlled trial (RCT), 120 MS patients will be randomised into one of three parallel groups: CRT, MBCT or enhanced treatment as usual (ETAU). Both CRT and MBCT consist of a structured 9-week program. ETAU consists of one appointment with an MS specialist nurse. Measurements will be performed at baseline, post-intervention and 6 months after the interventions. The primary outcome measure is the level of subjective cognitive complaints. Secondary outcome measures are objective cognitive function, functional brain network measures (using magnetoencephalography), psychological symptoms, well-being, quality of life and daily life functioning.

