### Objectives

This study primarily aims to examine the effectiveness of CRT and MBCT on subjectively experienced cognitive problems among MS patients. We hypothesise that both CRT and MBCT positively affect subjective cognitive function compared to enhanced treatment as usual (ETAU). We also expect positive effects on the secondary outcome measures objective cognitive function, functional brain network measures, psychological symptoms, well-being, quality of life and daily life functioning. Additionally, we will evaluate in an exploratory way whether there are differences in intervention effects between CRT and MBCT.

Secondary study objectives are:to explore the role of functional brain network measures (using MEG) in subjective and objective cognitive problems, and to evaluate whether there are differences in functional brain network measures between these types of cognitive problems;to explore the role of functional brain network measures as possible mediators in the effect of the interventions;to evaluate whether alterations in objective cognitive function, functional brain network measures, psychological symptoms, well-being, quality of life and daily life functioning are mediating factors that determine subjective cognitive function;to evaluate which factors determine whether a patient is likely to benefit from one of the therapies, such disease severity, severity of cognitive problems and mood at baseline, or gender.

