#### Primary and secondary objectives

To evaluate the effectiveness of the interventions, mixed-model analyses will be performed for the primary and secondary outcome measurements with time (baseline, post-intervention, follow-up) as a within subjects factor and condition (CRT vs. ETAU, MBCT vs. ETAU, and exploratory: CRT vs. MBCT) as a between-subjects factor. These analyses will be performed using an intention-to-treat approach, including all randomised participants regardless of adherence and measurement completion. Secondarily, per-protocol analyses will be performed for further exploration of the intervention effects.

To evaluate the secondary study aims, mediation and moderation analyses [61] will be performed to evaluate whether alterations in functional brain networks play a role in the effect of the interventions. In addition, cross-sectional associations between functional brain networks and cognitive function (subjective and objective) will be analysed using Pearson’s correlation and linear regression analyses. To evaluate whether alterations in secondary study parameters are mediating factors that determine subjective cognitive function, mediation analyses [61] and linear regression analyses will be performed. Finally, logistic and linear regression models will be performed to evaluate which factors determine whether a patient is likely to benefit from one of the therapies.

For all analyses, confounding variables will be inserted, such as age and education. Bonferroni corrections will be applied to correct for multiple comparisons within each objective.

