## Discussion

The best treatment options for cognitive problems in MS patients are still a matter of debate. This study will therefore investigate the effect of two promising non-pharmacological treatments: MBCT and CRT. To our knowledge, this will be the first RCT that investigates the effect of MBCT on cognitive function among MS patients. In addition, studying the effect of CRT on cognitive function may provide direction to the contradictory evidence that is currently available [12, 13]. If these treatments appear to be effective, we will investigate which factors predict this beneficial effect. These prognostic factors may lead towards tailored treatments for MS patients who suffer from cognitive problems.

An important strength of our study is that we use functional brain network measures, such as functional connectivity and nodal centrality, as an outcome variable. These measures may help to explain treatment effects and may provide information on whether network deterioration can be halted. Additionally, if functional brain network measures at baseline predict treatment outcomes, network analyses can be used as a prognostic factor. We will also relate functional brain network measures to objective and subjective cognitive problems in MS, which may help to understand the overlap and distinctiveness between these types of cognitive problems.

In summary, this study may help to unravel and treat cognitive problems among MS patients.

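### The choice of MEG methods and measures is deferred to study completion without masking, so the test of this secondary outcome is open to data-driven selection that the Bonferroni rule need not cover

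*Protocol article*

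**What the plan says.** The protocol article gives the MEG network measures the standing of a secondary outcome. The abstract states: "Secondary outcome measures are objective cognitive function, functional brain network measures (using magnetoencephalography), psychological symptoms". The Objectives section attaches a direction to them: "We also expect positive effects on the secondary outcome measures objective cognitive function, functional brain network measures". The Discussion counts it as a strength that "we use functional brain network measures, such as functional connectivity and nodal centrality, as an outcome variable". Under Statistical analysis, mixed models by intention to treat are planned for all primary and secondary outcomes, with CRT against ETAU and MBCT against ETAU as the main contrasts and CRT against MBCT as exploratory.

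The section Functional brain networks does not fix what the outcome is. For connectivity, "synchronisation measures will be computed, such as the phase-lag index". For the whole network, "Measures such as degree, clustering coefficient and path length will be computed". For the minimum spanning tree it adds betweenness centrality, tree hierarchy and eccentricity, again as examples. It announces an emphasis on node centrality without naming one measure. It then notes that the field is still developing and concludes that "the best methods and measures will be selected once the study is completed".

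On multiplicity, the section Primary and secondary objectives says: "Bonferroni corrections will be applied to correct for multiple comparisons within each objective". It gives no number of tests.

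**The concern.** This is not a detail left to another document. The article sets a time for the choice, and that time is after the data exist. It gives no criterion for what counts as best, and it does not say that those who choose will be masked to allocation or to results. The other secondary domains (cognitive tests, psychological symptoms, quality of life, well-being, daily functioning) all name their instruments; only the MEG outcome is left open.

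If several measures or processing methods are computed and the most favourable is reported, its nominal p-value no longer has its stated error rate. A Bonferroni correction repairs this only if its divisor includes the candidates that were computed and dropped. With an open candidate list, the divisor cannot be stated in advance. At stake is whether a reported benefit of CRT or MBCT on brain networks can be read as a test of the stated hypothesis.

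**Working it through.** The plan gives no figure to reproduce here. The following is an illustration under stated assumptions.

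**Inputs from the article**
- Named candidate measures: phase-lag index (1); degree, clustering coefficient, path length (3); betweenness centrality, tree hierarchy, eccentricity (3). Total 1 + 3 + 3 = 7. The lists are open, so 7 is not a ceiling.
- Main contrasts: 2.
- Alpha: .05, taken from the sample size section.

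**Assumptions not in the article**
- One test per measure and contrast, no true effect, and the best of the seven is kept.
- The Bonferroni divisor, varied below.
- The correlation between tests, varied below.

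**1. Best of seven, each at .05, one contrast.** Chance of at least one false positive = 1 − (1 − .05)^7 = 1 − .698 = .302 if the tests are independent. The named measures come from the same recordings, so correlation is likely. A simulation with 200,000 draws of equally correlated two-sided z tests gives:

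| Correlation | Chance of at least one false positive |
|---|---|
| 0 | .302 |
| .3 | .271 |
| .5 | .229 |
| .7 | .177 |

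**2. Divisor counts only the two contrasts of the measure kept.** Each test is at .05/2 = .025. Per contrast: 1 − .975^7 = .162. Over both contrasts (14 tests, treated as independent): 1 − .975^14 = .298.

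**3. Divisor spans the whole effectiveness objective, with MEG counted as one outcome.** One possible count is CFQ 1, BRIEF-A 2 (self and informant), cognitive tests 7, MEG 1, HADS 2, fatigue 1, brooding 1, quality of life 1, well-being questionnaires 3, daily functioning 2, which makes 21. With 2 contrasts the divisor is 42 and each test is at .05/42 = .0012.
- Best of seven, per contrast: 1 − (1 − .05/42)^7 = .008.
- Whole family: the other 20 outcomes × 2 contrasts, plus 7 MEG candidates × 2 contrasts, is 54 tests. 1 − (1 − .05/42)^54 = .062, against 1 − (1 − .05/42)^42 = .049 for the 42 tests counted.

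**4. Closed list, every candidate counted.** Seven tests at .05/7 = .0071: 1 − (1 − .05/7)^7 = .049. Fourteen tests (both contrasts) at .05/14 = .0036: 1 − (1 − .05/14)^14 = .049.

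The result therefore turns on the divisor. A narrow count leaves substantial inflation, a broad count leaves little, and a closed and fully counted list removes it. The article does not say which applies.

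**The case against.** The strongest reply is that the deferral has a scientific reason and that the text does not describe a choice made with results in hand. This is right as far as it goes. A reader might infer that the measures will be picked after unmasking, but the article does not say so. A choice made after the last visit by people masked to allocation and outcomes would fit its wording, and an SAP could specify exactly that. What remains is that the article promises no such masking, and its timing rule as written also permits the opposite.

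Three further replies are sound and limit the point.
- A reader might conclude that no correction could repair the problem. Step 4 shows otherwise: a closed list with all candidates counted holds the error. The defect is the open list and the unstated divisor.
- A reader might multiply 7 measures by 2 contrasts and 2 later time points to get 28 tests, and quote 1 − .95^28 = .76. That ignores the planned Bonferroni correction and assumes a separate test at each time point, which the mixed-model description does not state. It does not describe this plan.
- A reader might call every MEG result uninterpretable. The mediation aim is worded "to explore the role of functional brain network measures as possible mediators in the effect of the interventions", and the aim relating network measures to cognitive problems is likewise exploratory. Those uses already carry the appropriate caution.

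The emphasis on node centrality does narrow the field, but it names no endpoint. Pre-processing relies on available scripts from a cited source not to hand, so part of the pipeline may already be settled. Even so, the sentence defers methods as well as measures.

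**Conclusion.** The point holds for one use of the MEG data: the effectiveness test of the network measures as a declared secondary outcome with a directional hypothesis. As written, the plan leaves that test open to data-driven selection, and the Bonferroni rule does not protect it unless every candidate measure computed is counted. The CFQ primary outcome does not depend on which MEG measures are chosen.

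The size cannot be fixed from the article. Under a best-of-seven choice it runs, per contrast, from up to 30% with no correction (18% to 27% with correlations of .7 to .3), through up to 16% with a divisor of two, to under 1% with a divisor of 42. These are illustrations. Varying the processing methods as well would raise them, and a masked choice would remove the concern. The change should be made, but the point does not threaten the trial's main conclusion.

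**What to change.** Replace the deferring sentence with a statement that:
- the MEG processing pipeline and a short list of MEG outcome measures are fixed in a dated SAP before database lock, by people masked to allocation and outcome results;
- the multiplicity correction counts all MEG measures computed, and the SAP states the family and the divisor;
- any measure chosen or added after unmasking is reported as exploratory.

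The cost is a paragraph in the SAP and a lock date. New methods can still be adopted up to that date, so the reason given for waiting is respected. A list shorter than seven also keeps the per-contrast threshold above .0071. The only thing given up is the freedom to choose after unmasking.

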##### Psychological symptoms

Depression and anxiety are measured with the Hospital Anxiety and Depression Scale (HADS) [52]. The level of fatigue is measured with the Checklist Individual Strength-20-r (CIS-20-r) [53]. The tendency to ruminate when being sad or depressed is measured with the subscale ‘brooding’ of the Dutch Ruminative Response Scale (RRS-NL) [54].

##### Quality of life

Health-related quality of life is measured with the Multiple Sclerosis Quality of Life Questionnaire (MSQoL-54) [55].

##### Well-being

Emotional, psychological and social well-being is measured with the Mental Health Continuum-Short Form (MHC-SF) [56]. The ability to be mindful, that is, non-judgmental awareness of moment-to-moment experience, is measured with the Five Facets of the Mindfulness Questionnaire short form (FFMQ-SF) [57]. Self-compassion, that is, the ability to act with compassion towards oneself in difficult times, is measured with the short form of the Self-Compassion Scale (SCS-SF) [58].

##### Daily life functioning

Participation in society is measured with the Utrecht Scale for Evaluation of Rehabilitation – Participation (USER-P) [59]. Goal Attainment Scaling (GAS) is used to determine the effect of the treatment on personalised goals in daily situations [60].

### Randomisation and blinding

Following baseline assessment, participants will be randomly allocated to one of three treatment arms (MBCT, CRT or ETAU). First, the location of the intervention will be determined based on the patient’s living location and preference. For each location, randomisation will be performed in variable blocks of 6 and 9, and with an 1:1:1 allocation ratio. A minimisation program will be used to ensure balance between all groups. Minimisation will be performed on three factors: (1) subjective cognitive function, (2) age and (3) gender. Weighting is equal for each factor. The minimisation program will be constructed before the start of the study by an independent scientific programmer. The randomisation procedure will be performed by a researcher who is not involved in administering any outcome measure. Outcome measurements will be administered by assessors who are blind to treatment assignment, but this blinding is not feasible with regard to participants and therapists. Prior to each post-measurement, participants will be reminded not to disclose their group allocation to the assessor.

### Data management

The collected data will be labelled with a participant identification code. The name and other identifiers of the participant will be removed from the data. The link between the participant identification code and the names of the participants will be kept separately. An electronic case report form is developed according to the guidelines of Good Clinical Practice (GCP) to document the data collected in the study. This case report form will include demographic and clinical characteristics, and all outcomes of the study parameters. The data will be treated confidentially and will only be available to the trial coordinator and principal investigator. Other investigators can only get access to the data for the purpose of research and with permission of the principal investigator. The data gathered in this study will be protected in accordance with the Dutch Personal Data Protection Act and the Medical Treatment Contracts Act.

### Statistical analysis

#### Descriptive statistics

Data on demographic and clinical characteristics will be summarised in a table. For adherence and other feasibility indicators, frequencies and percentages will be calculated. Satisfaction with the program will be summarised in qualitative descriptions. Differences between groups (CRT vs. ETAU, MBCT vs. ETAU, CRT vs. MBCT, drop-outs vs. treatment completers) in demographic and clinical characteristics and outcome measurements at baseline are analysed using independent samples t-tests (normally distributed continuous outcome variables), Mann-Whitney U tests (skewed continuous outcome variables) and Pearson’s chi-square tests (categorical outcome variables).

#### Primary and secondary objectives

To evaluate the effectiveness of the interventions, mixed-model analyses will be performed for the primary and secondary outcome measurements with time (baseline, post-intervention, follow-up) as a within subjects factor and condition (CRT vs. ETAU, MBCT vs. ETAU, and exploratory: CRT vs. MBCT) as a between-subjects factor. These analyses will be performed using an intention-to-treat approach, including all randomised participants regardless of adherence and measurement completion. Secondarily, per-protocol analyses will be performed for further exploration of the intervention effects.

To evaluate the secondary study aims, mediation and moderation analyses [61] will be performed to evaluate whether alterations in functional brain networks play a role in the effect of the interventions. In addition, cross-sectional associations between functional brain networks and cognitive function (subjective and objective) will be analysed using Pearson’s correlation and linear regression analyses. To evaluate whether alterations in secondary study parameters are mediating factors that determine subjective cognitive function, mediation analyses [61] and linear regression analyses will be performed. Finally, logistic and linear regression models will be performed to evaluate which factors determine whether a patient is likely to benefit from one of the therapies.

For all analyses, confounding variables will be inserted, such as age and education. Bonferroni corrections will be applied to correct for multiple comparisons within each objective.

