#### Sample size calculation

Mixed model analyses will be applied with three measurements comparing two groups (MBCT vs. ETAU, CRT vs. ETAU). There are no previous studies with MS patients that investigated the effect of CRT or MBCT on the primary outcome measure, the Cognitive Failure Questionnaire (CFQ) [23]. Based on a previous RCT using a comparable outcome measure, a medium effect size can be expected [24, 25]. With an alpha of .05, a power of .80, an intra-class correlation of .06, and 33 participants per group, a minimal difference of 0.62 SD can be detected between two groups. Taking into account drop-out and loss to follow-up, we intend to recruit 40 MS patients per group.

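### Baseline is modelled as a level of the outcome with no common-baseline constraint or baseline adjustment stated, so a time-by-condition contrast with free baseline means loses a share (1 − r)/2 of the available precision

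*Protocol article*

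**What the plan says.** Under Statistical analysis, Primary and secondary objectives, the article sets one model for the primary and secondary outcomes: a mixed model with "time (baseline, post-intervention, follow-up) as a within subjects factor" and condition as the between-subjects factor. The section on sample size plans the same structure: "Mixed model analyses will be applied with three measurements comparing two groups".

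Under Randomisation and blinding, allocation comes after the baseline measurement: "Following baseline assessment, participants will be randomly allocated to one of three treatment arms (MBCT, CRT or ETAU". Allocation is minimised on subjective cognitive function, age and gender. The instrument behind the first of these is not named there.

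Covariates are given by example only (age and education). The article does not state a common baseline mean across arms, a baseline CFQ covariate, the model term that decides effectiveness, or the visit at which it is judged.

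**The concern.** Because allocation follows the baseline visit, the arms have the same expected baseline CFQ, and treatment cannot have affected it. A model that estimates a separate baseline mean for each arm ignores this. Its time-by-condition contrast then subtracts the whole observed baseline difference, where the efficient estimate subtracts only the part predicted by the correlation. The extra noise enters the standard error.

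The trial has little precision to spare. It plans 33 evaluable patients per arm for a detectable difference of 0.62 SD, and it intends Bonferroni correction within each objective. A baseline score that is already collected is the cheapest source of precision available.

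**Working it through.** **Inputs from the sample size section:** "With an alpha of .05, a power of .80"; "an intra-class correlation of .06"; "33 participants per group"; "a minimal difference of 0.62 SD can be detected between two groups". The article does not say whether alpha is two-sided (taken as two-sided here) or whether the intra-class correlation refers to visits within a patient or patients within a therapy group. The formulas below also assume equal variance at each visit, one common correlation r between visits, and complete data.

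**Formula.** Detectable difference in SD = (1.960 + 0.842) × √(2/33) × √V = 0.690 × √V.

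**The plan's own figure.** 0.62 SD needs V = (0.62/0.690)² = 0.81.
- Mean of three visits, r = .06: V = (1 + 2r)/3 = 0.373, giving 0.42 SD.
- Mean of two visits, r = .06: V = (1 + r)/2 = 0.53, giving 0.50 SD.
- One visit, no use of correlation: V = 1, giving 0.69 SD.
- .06 as clustering in therapy groups of 6 to 10: 0.74 to 0.86 SD, depending on group size and on whether one or both arms are clustered.
- r = .6: V = 0.80 gives 0.617 SD, either for the mean of two follow-ups, (1 + r)/2, or for change from baseline, 2(1 − r).

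The printed .06 therefore does not return 0.62 SD under these two-sided formulas, while r = .6 does. One-sided alpha .05 comes close by other routes (0.612 SD with V = 1; 0.611 SD baseline-adjusted at r = .06). The article does not settle which was meant, so r is treated as unknown below.

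**Reading A: time-by-condition contrast at one follow-up.**
- Baseline means free by arm: V = 2(1 − r).
- Baseline means constrained equal, or baseline as covariate: V = 1 − r².
- Ratio: (1 − r²)/[2(1 − r)] = (1 + r)/2. Share of precision lost: (1 − r)/2.

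| r | Share lost | Detectable difference, free | Detectable difference, adjusted |
|---|---|---|---|
| .06 (printed) | 47% | 0.946 SD | 0.688 SD |
| .2 | 40% | | |
| .5 | 25% | | |
| .6 (assumed) | 20% | 0.617 SD | 0.552 SD |
| .7 | 15% | | |
| .8 | 10% | | |

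At r = .6, power for 0.62 SD with 33 per arm is 0.804 free and 0.883 adjusted, and 33 against 27 patients per arm are needed. If Bonferroni over the two primary comparisons means alpha = .05/2 = .025, the detectable differences are 0.679 and 0.607 SD at r = .6, and 1.041 and 0.758 SD at r = .06.

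Generalised least squares on the three-visit model gives the same variances (0.80 free and 0.64 with a common baseline at r = .6; 1.88 and 0.9964 at r = .06). Both forms return the full treatment effect.

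**Reading B: condition main effect over all three visits.** The true effect is zero at baseline and, say, δ at both later visits. The estimate is (0 + δ + δ)/3 = 2δ/3, so 0.62 SD appears as 0.62 × 2/3 = 0.41 SD. At r = .6 the detectable true effect is 0.591 × 1.5 = 0.886 SD, and power at 0.62 SD is 0.50. At r = .06 these are 0.632 SD and 0.785.

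**The case against.** **Baseline as a level of time is not in itself wasteful.** This stands. The recommended model also keeps baseline in the outcome vector; the loss comes only from leaving its mean free by arm. The article does not say that the means are free. It says nothing on the constraint, and a full analysis plan that is not shown may supply it. The loss is therefore conditional.

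**The covariate list is open.** True, but a score already modelled as a response level cannot sensibly be added as a covariate of the same response, so the open list does not supply the adjustment.

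**Minimisation on subjective cognitive function already balances baseline.** This partly stands: chance imbalance should be smaller. But the instrument is not named, so balance on CFQ is not assured. Balance also does not narrow the standard error of an unadjusted model; it leaves that standard error too large.

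**The model is valid as it is.** This stands. Under randomisation the contrast is unbiased, and the point concerns efficiency only.

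**Stronger readings.** A reader might infer that every condition effect is diluted by a third and that 20% of the information is lost as well. The article does not support this. Dilution belongs to Reading B and the (1 − r)/2 loss to Reading A, so one analysis cannot suffer both. The article never says that the main effect is the test, and time-by-condition is the usual reading of such a design. Nor can 20% be stated as a fact about this trial: it needs r = .6, which the article does not give. That r = .6 reproduces the 0.62 SD does not show that a change score was planned, because the mean of two follow-ups fits equally well.

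**Conclusion.** The point holds as a conditional loss of efficiency in a valid analysis. With free baseline means and a time-by-condition test, the share of precision lost at one follow-up is (1 − r)/2, positive for every r below 1. It is 20% at an assumed r = .6, 10% to 40% for r from .8 to .2, and 47% if the printed .06 is the within-person correlation. These figures rest on equal variances across visits, complete data and two-sided testing. The direction is secure; the size depends on a correlation that the article does not establish.

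The claim that baseline adjustment brings the design back to about 0.62 SD at alpha .025 is also tied to r near .6 (0.607 SD); at .06 the figure is 0.758 SD. Reduction of the effect to two thirds is a separate possibility. It applies only if the main effect over three visits is tested, which the article neither states nor rules out.

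**What to change.** In the mixed model, constrain the baseline means to be equal across arms, include condition-by-time terms for the post-baseline visits, and use an unstructured covariance. Name the post-baseline visit that decides effectiveness, and take the condition contrast at that visit as the treatment effect. Do this for CFQ and for each secondary outcome measured at baseline.

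The constrained-baseline form is preferable to entering baseline CFQ as a covariate. The covariate form can drop patients with no post-baseline value, whereas the article commits to analysing everyone randomised, whether or not they completed the measurements. The constrained form keeps them and has the same variance as covariate adjustment at one follow-up (0.64 at r = .6).

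The cost is a change of wording in the analysis section before the data are analysed. No new data, visits or patients are needed. State the assumed within-person correlation at the same time, and reconcile the intra-class correlation of .06 with the 0.62 SD in the sample size section, so that the gain can be stated for this trial.
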